### Study hypotheses

1. Compared to participants receiving standard care, participants with diabetes and chronic kidney disease who receive the intervention will show greater reduction in blood pressure at three months post-intervention (T3).

2. Compared to participants receiving standard care, participants with diabetes and chronic kidney disease who receive the intervention will show a greater adherence to their prescribed medication regimen at three months post-intervention (T3).

3. Improved medication adherence will be associated with increased systolic blood pressure control at three months post-intervention (T3).

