### Patient eligibility

The inclusion criteria for the MESMI study are listed in Table 1. The primary outcome was systolic blood pressure control, taken by the research assistant who was trained to take blood pressure according to accepted guidelines [17] using an Accosson mercury desk sphygmomanometer and 3M™ Littmann classic 11 S.E. stethoscope. Participants were to avoid smoking, exercise and caffeine for 30 minutes while they were waiting for their clinic consultation and were seated for approximately five minutes prior to having their blood pressure measured.

**Table 1 T1:** Inclusion and exclusion criteria for the MESMI study

Inclusion criteria	
*****	Patients of either gender aged ≥ 18 years of age
*****	Able to comprehend English (English proficiency test > Not at all)
*****	Mentally competent (Abbreviated Mental Test score > 6)
*****	Type 1 or Type 2 diabetes recorded in patient's medical record
*****	Chronic kidney disease defined by an estimated Modified Diet in
*****	Renal Disease glomerular filtration rate (MDRD-eGFR) of ≤ 60 mL/min/1.73 m^2 ^and/or:
*****	Diabetic kidney disease defined by Malb/Cr ratios > 2.0 mg/mmol for men, > 3.5 mg/mmol for women or an elevated 24 hour urine albumin of > 30 mg over 24 hours
*****	Systolic hypertension ≥130 mmHg for the previous two clinic visits & prescribed antihypertensive medication/s
	

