### Data analysis

The analysis will be performed on an intent-to-treat basis. All data will be entered into an ACCESS database by a second research assistant who is blinded to the intervention group. An experienced biostatistician will check the integrity of the database and conduct statistical analyses. Descriptive statistics will be used to summarise demographic, social and medical data between the intervention and usual care groups and any effect of these variables on primary and secondary outcomes. Baseline characteristics of the intervention and usual care groups will be compared. Blood pressure, medication adherence, medication self-efficacy, and general wellbeing between the usual care and intervention groups will be compared to assess the effects of the intervention between groups and within participants at T2, 3 and 4 using t-tests as appropriate. The various measures of medication adherence will be examined for correlations. Continuous variables that are not normally distributed will be examined using equivalent non-parametric tests. Differences in change in binary categorical variables within each group will be analysed using McNemar's test and the changes between the two groups will be assessed by chi-squared tests for trends. Potential confounders may include comorbidities and number of prescribed medications. Statistical significance will be determined with p values of < 0.05.

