### Recruitment difficulties

The inclusion criteria presented difficulties, particularly in relation to pathology results recorded in the patient's electronic or hard copy of their medical record to determine eligibility. Although patients had diabetes and evidence of chronic kidney disease, patients did not routinely have microalbumin/creatinine ratios or less commonly, 24 hour urine albumins taken. Additionally, some estimated glomerular filtration rates were recorded as '≥ 60' or '< 90' depending on the point-of-care, and if patients did not have a microalbumin/creatinine ratio recorded in their history, they were excluded. Therefore, we have recruited participants with co-existing diabetes (Type 1 or 2) and microalbumin/creatinine ratios > 2.0 mg/mmol for men, > 3.5 mg/mmol for women or co-existing diabetes (Type 1 or 2) and chronic kidney disease (eGFR ≤ 60 mL/min/1.73 m^2^). The development, dissemination and implementation of chronic kidney disease clinical practice guidelines that harmonize with other specialties are needed to improve patient outcomes of chronic kidney disease [36]. We also changed the inclusion criteria to systolic hypertension ≥130 mmHg for the previous clinic visit rather than the previous two clinic visits to improve the rate of recruitment. These deviations and rationales have been documented with the ANZCTR. Our experience has shown that it is essential to pilot recruitment when funding limitations constrain the time period to run a RCT.

Another unforeseen problem affecting recruitment was a change in the organization of the diabetes outpatient clinics. Since commencing the study, patients with diabetes were 'handed over' to their general practitioners to manage in primary care rather than attend routine three monthly hospital outpatient clinic follow-up (these outpatient clinics were reduced to annual review), effectively reducing the pool of patients from which to recruit.

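### Before-after tests within an arm are named as a way to assess the intervention's effect, which only the randomised between-group comparison can do

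*Protocol article*

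**What the plan says.** In the protocol article, Methods, Data analysis, blood pressure, adherence, self-efficacy and wellbeing "will be compared to assess the effects of the intervention between groups and within participants at T2, 3 and 4 using t-tests as appropriate". For binary variables the plan is "Differences in change in binary categorical variables within each group will be analysed" with McNemar's test, and in the same sentence "the changes between the two groups will be assessed by chi-squared tests for trends". A single threshold of p < 0.05 applies to everything, and no test is marked as descriptive or subordinate.

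Elsewhere the plan is between-group. Hypotheses 1 and 2 (Study hypotheses) compare the intervention with standard care at T3, and the Power analysis section sizes the trial for a difference between groups. The Abstract, however, words the primary outcome as a fall of 3-6 mmHg with no comparator.

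On selection, Table 1 (Patient eligibility) requires "Systolic hypertension ≥130 mmHg for the previous two clinic visits & prescribed antihypertensive medication/s". Recruitment difficulties reports that this was relaxed to a reading "for the previous clinic visit rather than the previous two clinic visits". The T1 baseline pressure is a new, averaged reading at a later home visit, for which no threshold is stated (Enrolment and randomization).

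**The concern.** The t-test sentence gives between-group and within-participant comparisons equal standing as ways to assess the intervention. Only the first does so. A paired test in the intervention arm answers whether that arm changed, not whether the intervention changed it.

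Several things could move both arms together: passage of time, repeated home visits with pressure readings and pill counts by a research nurse, being asked to keep empty containers, and whatever regression to the mean is left after selection on systolic pressure. If within-arm p-values are reported as evidence, a result that is significant with the intervention but not with usual care can be read as an effect when there is none. The Abstract's wording of the primary outcome as a drop makes that reading easier.

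A second, smaller matter is the between-group test for binary change. If change is scored as worse, same or better, someone adherent at both visits gets the same score as someone non-adherent at both. That discards information the trial has collected.

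**Working it through.** **1. The plan's own figure is for the between-group contrast.** Inputs from Power analysis: SD 12.1 mmHg, one-tailed alpha 0.05, 80% power, 5% attrition. At the 6 mmHg end of the stated range:

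n = 2 × (1.645 + 0.842)² × 12.1² / 6² = 50.3, so 51 per group; 51 / 0.95 = 53.7, so 54 per group and 108 in all.

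This reproduces the stated 51 and 108. Nothing in the size of the trial depends on a within-arm test.

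**2. What a shared fall does to within-arm tests (illustration).** Inputs: 51 per arm; SD of change 12.1 mmHg (an assumption, equal to the protocol's SD if visits correlate at 0.5); two-sided paired t-test at 0.05; the same fall in both arms, so no intervention effect. The size of the fall is assumed.

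SE = 12.1 / √51 = 1.694. For a 3 mmHg fall the noncentrality is 3 / 1.694 = 1.77, and the probability p of a significant fall in one arm is 0.412. Intervention arm only: p(1 − p) = 0.412 × 0.588 = 0.242. Exactly one arm: 2 × 0.242 = 0.484.

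| Shared fall (mmHg) | Significant in intervention arm only |
|---|---|
| 0 | 2.4% |
| 1 | 7.7% |
| 2 | 16.7% |
| 3 | 24.2% |
| 4 | 23.1% |

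**3. How much of a shared fall could be regression to the mean.** Simulation with no intervention effect, 51 per arm, SD 12.1, population mean 130 mmHg (Feasibility of study puts about 50% above 130) and selection at ≥130. Assumed: visit-to-visit correlation 0.5 to 0.7. The ranges cover both the one-visit and two-visit rules.

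- Baseline is the separate T1 reading, with error independent of the qualifying reading: mean change about 0; within-arm t-test shows a fall in about 2-3% of trials, against a nominal 2.5% in that direction.
- T1 error correlated 0.3-0.5 with the qualifying reading (assumed): spurious fall 0.6-2.4 mmHg; within-arm fall significant in 8-29% by t-test and 4-19% by McNemar's test on systolic pressure ≥130.
- Between-group t-test on change: about 4-6% in every scenario, against a nominal 5%.

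**4. Efficiency of a trend test on binary change.** Score change as -1/0/+1 (an assumption; the article gives no scoring). With equal prevalence at both visits and correlation ρ between them, the variance of change is proportional to 2(1 − ρ), and the variance after adjusting for baseline to (1 − ρ²). The ratio of adjusted to change-score variance is (1 + ρ)/2. At ρ = 0.4 it is 0.70.

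Worked case with assumed rates: half adherent at baseline; in usual care 70% of these stay adherent and 30% of the others become adherent (which gives ρ = 0.4); odds ratio 3 for the intervention. The intervention probabilities are then 87.5% and 56.25%, so T3 adherence is 50% against 71.9%, a difference of 0.219.

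- Change score: variances 0.300 and 0.296; SE = √(0.596/51) = 0.108; z = 2.02; power about 53%.
- Stratified on baseline: average variances 0.210 and 0.178; SE = √(0.388/51) = 0.087; z = 2.51; power about 71%.

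Simulations at 51 per arm, under assumed effects, gave 46-62% for the trend test and 67-76% for the stratified comparison, with type I error near 5% for both.

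**The case against.** The randomised comparison is already planned. The sentence that mentions within-participant tests also compares the groups, the McNemar sentence goes on to a between-group test, and both the hypotheses and the sample size are between-group. The plan nowhere says that significance in one arm only will count as evidence, so the 24% and 48% figures describe an inference the document does not commit to. This stands: they illustrate a risk of interpretation and are not an error rate of the plan.

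A reader might go further and infer that selecting people at ≥130 mmHg, relaxed to one visit, makes regression to the mean appear as benefit. Had the qualifying clinic reading been the baseline, the same simulation would give a spurious fall of 2.9-4.8 mmHg under the one-visit rule. But T1 is a fresh home reading, so much or all of that regression can happen before baseline. Moving from two visits to one matters only as far as error carries over into T1. Selection on pressure also has no direct bearing on adherence, self-efficacy or wellbeing. This objection stands as well.

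The McNemar sentence does not say that it assesses effect; only the t-test sentence does. And the trend test is valid under randomisation, so replacing it gains efficiency and corrects no bias. Both are fair. None of this turns a within-arm p-value into evidence of effect, which the t-test sentence expressly allows.

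**Conclusion.** The point holds as one of wording and interpretation, with a free gain in efficiency for the binary outcomes. The plan names within-participant tests as a way to assess the intervention's effect, and they cannot do that.

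The documents do not support the stronger reading that the primary comparison is biased. Under no effect the between-group test keeps its level (about 4-6%), and randomisation balances regression to the mean across arms.

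The size of the within-arm problem depends on a shared change that the documents do not give. It is nil if nothing moves both arms, and about 24% for significance in the intervention arm only under an assumed 3 mmHg fall. That assumed fall lies above the 0.6-2.4 mmHg that regression to the mean gave with correlated T1 error, so it would need other shared causes. The efficiency gain (roughly 46-62% to 67-76% power) rests on the assumed scoring, adherence rates and effect.

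**What to change.** In Data analysis:

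- Delete within-participant comparison as a basis for assessing effect, and state that effect is judged only by the randomised between-group comparison.
- Report within-arm changes descriptively, without p-values.
- For binary outcomes such as ≥80% adherence and systolic control, replace McNemar's test plus the chi-squared test for trend with a between-arm comparison at T3. Adjust it for baseline status and the stratification factors (age, gender, baseline systolic pressure), for example by logistic regression, and report it with a 95% CI.

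The cost is a change of analysis wording. The data are already in the collection schedule (Table 2), and the 51 per group was computed for the between-group contrast, so the sample size does not change.

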## Discussion

This trial involves an evaluation of the effectiveness of a multifactorial intervention developed from analysis of medication adherence from the perspectives of consumers with co-existing diabetes and chronic kidney disease and multidisciplinary health professionals likely to be involved in their management. This approach was chosen to foster effective communication and partnerships with health professionals necessary for improved medication adherence and patient health outcomes. The major strength of this trial is that it is one of the first published studies to tackle the problem of competing comorbidity management where consumers are required to consult with multiple health practitioners and take multiple prescribed medications.

### Recruitment difficulties

The inclusion criteria presented difficulties, particularly in relation to pathology results recorded in the patient's electronic or hard copy of their medical record to determine eligibility. Although patients had diabetes and evidence of chronic kidney disease, patients did not routinely have microalbumin/creatinine ratios or less commonly, 24 hour urine albumins taken. Additionally, some estimated glomerular filtration rates were recorded as '≥ 60' or '< 90' depending on the point-of-care, and if patients did not have a microalbumin/creatinine ratio recorded in their history, they were excluded. Therefore, we have recruited participants with co-existing diabetes (Type 1 or 2) and microalbumin/creatinine ratios > 2.0 mg/mmol for men, > 3.5 mg/mmol for women or co-existing diabetes (Type 1 or 2) and chronic kidney disease (eGFR ≤ 60 mL/min/1.73 m^2^). The development, dissemination and implementation of chronic kidney disease clinical practice guidelines that harmonize with other specialties are needed to improve patient outcomes of chronic kidney disease [36]. We also changed the inclusion criteria to systolic hypertension ≥130 mmHg for the previous clinic visit rather than the previous two clinic visits to improve the rate of recruitment. These deviations and rationales have been documented with the ANZCTR. Our experience has shown that it is essential to pilot recruitment when funding limitations constrain the time period to run a RCT.

Another unforeseen problem affecting recruitment was a change in the organization of the diabetes outpatient clinics. Since commencing the study, patients with diabetes were 'handed over' to their general practitioners to manage in primary care rather than attend routine three monthly hospital outpatient clinic follow-up (these outpatient clinics were reduced to annual review), effectively reducing the pool of patients from which to recruit.

At recruitment, we found a significant number of participants spoke a language other than English, most commonly Greek and Italian, who were excluded from the trial because they did not speak English. The latest Australian census shows that one quarter of Australians are born overseas [37], and consumers from culturally and linguistically diverse backgrounds have an increased risk of medication mismanagement [38]. In addition, 123 patients who met the inclusion criteria refused the opportunity to participate and a further 40 patients who met the inclusion criteria did not turn up for their scheduled appointment. A run-in period would have alerted us to these difficulties and enabled us to introduce strategies to enhance recruitment, such as clinic appointment reminders and reimbursement for participation.

